### C. Population Size Estimate Analysis

#### Population Size Estimation Analysis using PLACE

1. For each area that was mapped, we will estimate the number of sites in each area by type of site and type of key population at site
2. We will estimate the number of each type of key population at each type of site
3. We will provide a map of sites indicating the number of key populations at each
4. We will estimate the total number of key population member in each zone and in the sub-national areas included in the estimate
5. We will extrapolate the estimate to include areas not covered
6. We will estimate the number of key populations missing from the estimate based on findings from formative research
7. We will refine the size estimates based on mobility of key populations, visits to multiple venues, and variety in frequency of attendance
8. We will use the size estimates to calculate coverage for components of the comprehensive program for key populations

The following steps for size estimation will be followed:

1. Review data to confirm completeness of site lists and adequacy of estimates of the number of key population members at each site. Check the quality of the data by comparing the number of sites named and the number of times each was named with the number of reports naming a site from community informants. Check that there are sites named in every area included in the mapping activity. Confirm that the interviewers included members of each key population and that targets for type and number of community informants were reached. Review the list of sites that were not located and re-visit a random sample to confirm that the sites do not exist.
2. Calculate a point estimate for the number of each key population at each site based on the reported range provided. At each site, informants will be asked to estimate the maximum and minimum number of key populations at the site at a busy time.
3. Separate the estimates from sites that were initially identified as sites with key populations from sites that were not reported to have key populations. The rationale for treating the two types of sites differently is that they are sampled with different sampling fractions and the expected number of key populations at the sites reported to have key populations will be higher than at the other sites.
4. Add up the median number of key populations at each site for an initial crude estimate of the size of each population.
5. Produce a map illustrating number of key populations at each site using the median for the size estimate.
6. Adjust estimates based on information about frequency of visiting sites, frequency of visiting more than one site in a day, and the percentage of sites that have key populations but were not initially identified as sites with key populations.
7. Use the formula below to estimate the size based on the key population sites and separately for the other sites. The formula is:

$$E_i = s_i(1-p_i) + (s_i * p_i / m_i)$$

$E_i$  = the estimated key population members in an area

$s_i$  = estimate at the site level

$p_i$  = Proportion of female sex workers solicit in two or more sites

$m_i$  = Mean number of places a female sex worker solicit

For example,

If  $s_i$  from all the key population sites is 10,000 and 10% solicit in other sites, and the mean number of places the 10% solicit is 2 then the estimate is

$$10,000 (1 - 0.1) + (10,000 * 0.1 / 2)$$

$$= 9000 + 10,000 * 0.05$$

$$= 9000 + 500$$

$$= 9500$$

The formula is reasonable because it counts all of who are only at one place and for the ones who go to more places, the percentage of that group is reduced because the people might have counted at more than one place. This could be repeated for key populations at Other Sites. If 500 were found at Other Sites, the estimate would be 10,000.

8. Use the area estimates to develop national estimates. National estimates are developed by extrapolation of data. One approach is to estimate the percentage of the male and female population who is a member of a key population in the areas where the mapping and size estimation activity was done. Apply the percentage estimated in one area to the areas that are similar.
9. Meet with stakeholders to review the estimates and ensure that the size estimates are reasonable and acceptable to the stakeholders.
10. The size estimates can be used as the denominator in coverage estimates. If the randomly selected members of the key population were asked questions about access to testing and other prevention initiatives, additional analysis of their responses would be useful.

Size estimates of populations at risk for HIV/AIDS infection help policy makers and program administrators understand the scope of the HIV problem, plan appropriate interventions, and allocate sufficient resources. Population size estimates will be used as denominators in calculating program coverage and producing estimates and projections of the HIV epidemic in areas where calculated. The data are intended to be used by the MoH, non-governmental organizations (NGOs), and other stakeholders for disease control purposes, specifically for program coverage planning and assessments.

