#### *Ethical Considerations for Venue Visits and Mapping*

Because knowledgeable people interviewed at venues are only asked questions about the venue and not about their personal behavior, there is no personal risk involved in this phase of data collection. No personal identifying information is collected from the respondent.

Maps made using the data from this phase of data collection will not indicate the location of vulnerable populations such as sex workers, MSM and transgender women. Venue maps will only indicate the distribution of venues and the coverage of prevention programs. Maps of priority venues for interventions may include venues where sex workers, MSM and transgender women visit, however the presence of specific populations will not be indicated.

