#### *Consent Process for Venue Visits and Mapping*

Interviewers will explain to **site informants** the purpose of the study, type of questions asked, and that no identifying information will be collected from them. Site informants will not require formal consent as the data collected from these informants is unrelated to their personal characteristics and is centered on the PPA and/or venue of interest. Site informants will receive a fact sheet about the study will contact number for the local and UNC researchers.

Knowledgeable people at venues are not asked any personal information. They are asked their age in order to confirm eligibility (age 18 or older are eligible). Once eligibility is determined, the interviewer will read a short description of the study and the type of questions that will be asked.

*“Hello. My name is \_\_\_\_\_ and I am working with Tchikos/the National Institute against HIV/AIDS the national on a study that will improve HIV prevention programs here. I would like to ask you some questions about this place to find out about people who come here to socialize or meet sex partners and about HIV prevention that has occurred here. I can offer you this Fact Sheet that has more information about the study.”*

The interviewer will offer the respondent a Fact Sheet (see Appendix 8) that contains information about the study, including contact information within Angola in case questions arrive after the interview. Next, the interviewer asks if they are willing to participate. If they are willing, the interview begins.

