|----------------------------------------------------------------------------------------------------------------------------|-------------------------------------------------------------------------------------------------------------------------------------------|----------------------------------------------------------------------------------------------------------------------------------------------------------------------------------------------------------------------------------------------------------------------------------------------------------------------------------------------------------------------------------------|
| B25                                                                                                                        | In the past 12 months have you...                                                                                                         | 
Yes    No
 
A. Sold sex for money?    1    2
 
B. Sold sex for goods or favours?    1    2
 
C. Injected drugs without a prescription?    1    2
 
MEN ONLY: Had sex with another man?    1    2
 |
| B26                                                                                                                        | INTERVIEWER OPINION:
HOW KNOWLEDGEABLE IS THIS
RESPONDENT LIKELY TO BE ABOUT
THE ACTIVITIES AND PATRONS AT THE
SITE OR EVENT? | 
Extremely knowledgeable    1
 
Knowledgeable    2
 
Not very knowledgeable    3
                                                                                                                                                                                          |

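### The protocol promises that venue maps will not show where key populations are and that venue informants are asked nothing personal, but the analysis plan orders per-site maps and Form B asks informants about their own behaviour

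*Protocol*

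**What the plan says.** **Maps.** The Protocol, Ethical Considerations for Venue Visits and Mapping (section VI.C, Step 3), states: "Maps made using the data from this phase of data collection will not indicate the location of vulnerable populations", and names sex workers, MSM and transgender women as examples. It allows maps of priority venues to include places these groups visit: "however the presence of specific populations will not be indicated". Section VIII.C, Population Size Estimation Analysis using PLACE, item 3 of the first list, states: "We will provide a map of sites indicating the number of key populations at each". Step 5 of the second list repeats the order.

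**Venue informants.** The same ethics section says that informants are "only asked questions about the venue and not about their personal behavior", and concludes that they run no personal risk. Consent Process for Venue Visits and Mapping waives formal consent on the ground that the data do not concern the informant, and adds: "Knowledgeable people at venues are not asked any personal information". Age, for eligibility, is the only exception it gives. Form B (Appendix 3) asks informants how they describe their sexual or gender identity (B24). B25 then asks whether in the past 12 months they sold sex for money or for goods or favours, "Injected drugs without a prescription" or, for men, had sex with another man.

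**The concern.** Both contradictions concern protections given to people in stigmatised groups. Site-level maps of these groups fall under the misuse of spatial data that the mapping readiness assessment in Appendix 1 is meant to guard against. If the size estimation steps are followed as written, the team produces the kind of map that the ethics section rules out.

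On Form B, both the statement of no personal risk and the waiver of formal consent rest on the absence of personal questions. If the form is used as printed, that premise is false, and stigmatised behaviour is recorded under a procedure justified for venue facts only.

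**Working it through.** The check is of text against text. The only arithmetic is the count of interviews.

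**1. Are these the same data?** Yes. Step 2 of the size estimation steps gives the source of the counts: "At each site, informants will be asked to estimate the maximum and minimum number of key populations at the site at a busy time". The informants at each site are the Step 3 venue informants. Form B collects their counts of others at the site (B6, B9, B13 to B15) and the site's GPS coordinates (Q8). The ethics promise covers maps made from the data of that phase, so the promise and the plan cannot be assigned to different maps.

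**2. Does a count at a site show location?** Step 5 reads: "Produce a map illustrating number of key populations at each site using the median for the size estimate". A non-zero count at a mapped venue shows that members of these groups are found there. This holds even if the three groups are pooled into one number.

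**3. Is there a limit that would reconcile the two?** Neither item 3 nor step 5 restricts the map to internal use, masks locations or aggregates them. The paragraph closing that section names the ministry, non-governmental organisations and other stakeholders as intended users of the size estimates.

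**4. What does Form B ask about the informant?** Beyond age:
- whether the informant works there, sex at birth and current gender (Q13 to Q15);
- how many other places the informant visited that day to socialise, drink or look for a sex partner (B3B);
- sexual or gender identity (B24);
- own sale of sex, injecting and, for men, sex with men (B25).

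Any yes in B25 leads to a Part III (B27). The instructions to Form B prefer a key-population member as informant, so a yes is to be expected often. The answers stand on the same form as the site name, address and coordinates.

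**5. What consent applies?** The consent section requires only a fact sheet and a willingness question. Q10B asks the interviewer whether a consent form was read. The form and the section disagree. Written consent and a private place are specified in Step 4 for patrons and workers, not for venue informants.

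**6. How many interviews?** The venue-informant row of Table 3 gives Luanda 700, Benguela 500, Bié 500, Cunene 500 and Cabinda 0.

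700 + 500 + 500 + 500 + 0 = 2,200

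The printed total is 1,500, which equals 500 + 500 + 500 and so leaves out Luanda.

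**The case against.** The strongest reply is that counting the people who can be reached at each site is a stated purpose of programmatic mapping (Appendix 1). The readiness assessment also asks what can prevent misuse of maps, requires an action plan for each risk and can stop the mapping. Access to data is limited to authorised staff, and no identifying information is taken from informants. All of this is in the protocol. None of it qualifies the promise about maps or makes the description of Form B true. It does show that restricting circulation, or rewriting the ethics and consent text, would also reconcile the passages.

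A reader might infer more than the documents support:
- **A public map, or one by population type.** Item 3 and step 5 name no audience and do not say whether the groups are shown separately. With a pooled map the conflict is clear for the promise on location, less so for the clause on specific populations.
- **Personal questions on a fact sheet alone.** Q10B refers to a consent form, and Part III does not appear in Appendix 3 as shown. It may be the section of Form C for key-population members, whose respondents give written consent. The fact sheet and consent forms were not available for this check, so what informants are told cannot be judged.
- **About 2,200 mapped points.** The figure is planned interviews. Form B Q7 allows for sites not found, closed, refused or duplicated, and site types include websites and phone services.
- **Loss of ethics approval.** Nothing in the documents says so, and Form B is an appendix to the protocol that goes to both review bodies.
- **Bias from under-reporting.** No described analysis uses B24 or B25. The size estimates use informants' counts of other people.

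**Conclusion.** The point holds in both parts. The size estimation plan orders a map that the ethics section excludes, from the same data and with no limit on circulation. Form B collects personal behaviour and identity under a consent waiver that rests on none being asked, and its own consent item does not match the consent section.

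The scope is the venue phase in four provinces, with up to 2,200 planned interviews. That number is a ceiling for interviews and is not a count of mapped venues or of sensitive answers. No estimator, sample size or reported indicator changes. The point warrants correction before field work because explicit participant protections are contradicted by planned procedures and the correction is cheap.

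The conclusion rests on the text of the ethics, consent and size estimation sections and of Form B as printed. It assumes nothing about the content of the fact sheet, the consent forms or Part III.

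**What to change.** **Maps.** Change item 3 and step 5 of Population Size Estimation Analysis using PLACE to maps by zone. Item 4 of the same section already estimates totals by zone, so no new analysis is needed. Keep site-level counts in the access-restricted dataset. Reword the ethics paragraph to say that numbers are shown by zone only, since read literally it bars any indication of location.

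**Form B.** Choose one of two courses:
- drop the personal items B3B, B24 and B25, with the linked B27 and B28; or
- keep them, but ask them only in private and after the written consent used for Form C.

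In either case correct the ethics and consent sections and Q10B so that they describe the same procedure and acknowledge whatever personal items remain, including Q13 to Q15. Correct the Table 3 total to 2,200, or correct the row if 1,500 was meant.

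**Cost.** No site-level map of numbers circulates; programmes that need site detail would have to receive it under restricted access. If B24 and B25 are dropped, Form B no longer records whether the informant belongs to a key population, although such informants are preferred. If they are kept, the venue interview needs a private place and a written consent step.

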**Table 3 Summary of interviews to be completed by province**

| Population                                      | Luanda | Benguela | Bié | Cunene | Cabinda | Total |
|-------------------------------------------------|--------|----------|-----|--------|---------|-------|
| Community informant interviews                  | 500    | 500      | 500 | 500    | 0       | 2000  |
| Venue informant interviews                      | 700†   | 500      | 500 | 500    | 0       | 1500  |
| Behavioral interview and HIV/STI testing |        |          |     |        |         |       |
| Female sex workers                              | 600    | 400      | 400 | 400    | 400     | 2200  |
| Men who have sex with men                       | 600    | 400      | 400 | 400    | 0       | 1800  |
| Transgender women                               | 200*   | ‡        | ‡   | ‡      | 0       | 200*  |
| Other men and women at venues                   | ‡      | ‡        | ‡   | ‡      | 0       | ‡     |

\* Could be less based on the number and percent of people at venues who identify as transgender, has received money for sex and who are men who have had sex with a man in past 12 months. † If there are more than 700 venues are identified in Luanda, a sample of venues will be selected. \*\*The sample must be confirmed by UNC staff prior to field work. \*\* ‡ No defined sample size as sample will depend on distribution of key populations in venues sampled.

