## ***F. Population Size Estimation Procedures***

### ***PLACE-Programmatic Mapping Population Size Procedures***

The process is to estimate the number of each type of key population at each site, sum up the estimates across all of the sites, adjust the estimate to take into account visits to multiple sites and mobility, and finally extrapolate the number to areas not covered by the mapping.

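### The PLACE size estimate adds site counts without inverse-fraction weights, although the protocol says its two site strata are sampled at different fractions

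*Protocol*

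**What the plan says.** Section VI.F (PLACE-Programmatic Mapping Population Size Procedures) gives the order of work: estimate the number at each site, then "sum up the estimates across all of the sites, adjust the estimate to take into account visits to multiple sites and mobility", and finally extrapolate to areas the mapping did not cover.

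Section VIII.C (Population Size Estimation Analysis using PLACE) sets this out in ten steps:

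- **Step 2** gives the source of the counts: "At each site, informants will be asked to estimate the maximum and minimum number of key populations at the site at a busy time". A site has a count only if a Form B interview was held there.
- **Step 3** keeps key-population sites apart from other sites, partly because "they are sampled with different sampling fractions".
- **Step 4** is the aggregation rule: "Add up the median number of key populations at each site for an initial crude estimate of the size of each population".
- **Step 6** adjusts for how often people visit sites, for visits to more than one site in a day, and for the share of sites with key populations that had not been reported as such.
- **Step 7** gives E = s(1 − p) + s·p/m and a worked example that reaches 9,500 for key-population sites. It continues: "If 500 were found at Other Sites, the estimate would be 10,000".
- **Step 8** carries area estimates to similar areas and to national level.

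The footnote to Table 3 in section VI.E adds: "If there are more than 700 venues are identified in Luanda, a sample of venues will be selected".

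**The concern.** A total over sampled sites needs each count divided by the site's chance of being in the sample. The protocol recognises unequal fractions and uses them only to keep the two strata separate. Keeping them separate does not correct either sum, because the two results are then added. The example does this one for one, taking what was observed at Other Sites as that stratum's contribution.

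The sizes serve as denominators for programme coverage and feed the extrapolation in step 8. A denominator that is too low makes coverage look too high. Step 8 applies the mapped areas' percentage elsewhere, so it would carry the shortfall forward. Strata summed at different fractions would also not be on the same footing.

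**Working it through.** **Inputs.** s = 10,000, p = 0.10, m = 2 and 500 at Other Sites come from the step 7 example. The 700-venue threshold comes from the Table 3 footnote. The protocol gives no values for the sampling fractions, so every f below is an assumption.

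**1. The protocol's own figure.** E = 10,000 × 0.9 + 10,000 × 0.1/2 = 9,000 + 500 = 9,500. Adding 500 gives 10,000. Both figures reproduce.

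**2. What the formula corrects.** E = s(1 − p + p/m), which here is 0.95 s. It is proportional to s and contains only p and m. If s is an unweighted sum over a fraction f of the sites, E is low by the same factor f.

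**3. The example with expansion.** T = 0.95 × 10,000/f_KP + 500/f_other.

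| f_KP (assumed) | f_other (assumed) | T | Shortfall of 10,000 against T |
|---|---|---|---|
| 1 | 1 | 10,000 | 0% |
| 1 | 0.5 | 9,500 + 1,000 = 10,500 | 4.8% |
| 1 | 0.25 | 9,500 + 2,000 = 11,500 | 13.0% |
| 1 | 0.2 | 9,500 + 2,500 = 12,000 | 16.7% |
| 1 | 0.1 | 9,500 + 5,000 = 14,500 | 31.0% |
| 0.7 | 0.25 | 13,571 + 2,000 = 15,571 | 35.8% |

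**4. Luanda under the Table 3 footnote.** Assume an equal-probability draw of 700 venues and the same mean count at visited and unvisited listed venues. The share of the total captured is 700/N for N > 700.

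| Venues identified, N | Share captured | Shortfall |
|---|---|---|
| 700 or fewer | 100% | 0% |
| 800 | 87.5% | 12.5% |
| 1,000 | 70% | 30% |
| 1,400 | 50% | 50% |

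**5. Does another step supply the fraction?**

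- The step 6 percentage is a prevalence of key populations among other sites. It is not the share of those sites that was visited.
- Step 7 only removes double counting.
- Item 5 of the outline that opens the section, and step 8, extrapolate to areas that were not mapped. They do not cover unvisited sites inside a mapped area.
- Outline item 1 promises an estimated number of sites by type, but no step links that number to s.
- Outline item 6 draws the missing population from formative research, which cannot supply the fractions of a later venue draw.

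**The case against.** The best defence is that the protocol never says unvisited sites count as zero. Section VI.F speaks of summing over all sites. Step 4 is labelled a first crude figure. Outline items 1, 2 and 4 (sites by type, numbers per type of site, then the total) have the shape of an expansion. Weight formulas are often left to an analysis plan, and section VIII.B already commits the PLACE surveys to weights. Step 3 also does not say at which stage its fractions apply; the venue sampling described in section VI.C, Step 4 is for patron and worker interviews, not for Form B.

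Part of this stands:

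- The only sampling explicitly stated for the venue-informant visit is in Luanda, and only above 700 venues. If every listed site is visited, this source of error is nil.
- The 10,500 and 12,000 rest on assumed fractions.

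The rest does not repair the rule. The protocol chose to fix the steps, formula and example itself, and none of them carries a fraction. The outline items are never tied to s, and the section VIII.B weights are described for survey indicators.

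A reader might go further and infer three things that the documents do not support:

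- **That the final population figure is understated.** Counts are informants' busy-time guesses, later adjusted for attendance and multi-site visits, so the net direction is open.
- **That every refusal becomes a zero.** The Form B instructions replace a respondent who refuses, so only sites finally coded as declined lack a count.
- **That closed sites are wrongly omitted.** Permanently closed sites properly count zero. Only temporarily closed ones, which section VI.C keeps in the interview frame, lack a rule.

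**Conclusion.** The point holds as a defect in the stated rule. Section VIII.C acknowledges different sampling fractions and then sums site counts without using them. Wherever f is below 1 in a stratum, that stratum's sum is f times what it should be, assuming equal-probability selection within the stratum.

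In Luanda the effect is conditional on the number of venues identified: nil up to 700, and 12.5% or 30% at 800 or 1,000. In the protocol's example the total would rise by 500 or 2,000 if Other Sites were visited at 1 in 2 or 1 in 5 and key-population sites in full. These are errors in one component; the bias of the final estimate is not established. A smaller gap of the same kind is that existing sites without a count have no stated treatment.

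**What to change.** **Steps 4 and 7.** Define s, within province and stratum, as the sum of site counts, each multiplied by the inverse of the site's probability of selection for a Form B visit. With an equal-probability draw this is sites listed divided by sites selected. Selected sites that prove not to exist, to be permanently closed or to be duplicates count zero, so unvisited names are discounted at the observed verification rate.

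This detail matters. Suppose 1,000 sites are listed, 700 are visited and 100 of those are not found or are duplicates. The inverse fraction is 1,000/700 = 1.43. A weight that took every unvisited name as a real, unique site would be (600 + 300)/600 = 1.50, about 5% too high.

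**Existing sites without a count.** For temporarily closed sites and those finally coded as declined, apply a stratum-level non-response factor. Form B has a single code for a closed location, so it must be split into temporary and permanent.

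**Worked example.** Restate it so that the 500 at Other Sites is an expanded figure, with the fraction shown.

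**Cost.** Analysis wording, one weight per stratum (or per site if the draw is unequal), one extra Form B code, and a record of how venues are drawn. The site lists and most of the visit outcomes are already captured on Forms A2 and B.

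### The PLACE size formula applies a person-level proportion to a sum of site-level counts, and its worked example defines the mean number of sites differently from the formula

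*Protocol*

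**What the plan says.** The Protocol's section on population size estimation using PLACE (VIII.C) gives ten numbered steps for the estimate. Step 4 builds the crude total: "Add up the median number of key populations at each site for an initial crude estimate of the size of each population". Step 7 then adjusts it for women who use more than one site: "Use the formula below to estimate the size based on the key population sites and separately for the other sites". The formula is E = s(1-p) + s*p/m, with these definitions:

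- s: "estimate at the site level"
- p: "Proportion of female sex workers solicit in two or more sites"
- m: "Mean number of places a female sex worker solicit"

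The worked example takes s = 10,000 and p = 10%, describes m as "the mean number of places the 10% solicit is 2", and obtains 9,500. The text justifies shrinking the multi-site part "because the people might have counted at more than one place". Step 8 extrapolates the area estimates nationally, and step 10 allows the sizes to serve as coverage denominators.

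**The concern.** p and s are on different scales. p is a proportion of women. s is a total of counts, and a woman who uses several sites can add more than one to it. Multi-site women therefore make up a larger share of the counts than of the women. Applying the person share to the counts treats too few of them as duplicates, so the adjusted size stays too high. The shortfall grows with movement between sites, which is what step 7 is meant to correct.

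The symbol m has a separate problem. Its definition covers all female sex workers, while the example averages over the multi-site women only. Two analysts following the text could obtain different answers from the same data.

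At stake are the size estimates, their extrapolation, and the coverage figures that use a size estimate as denominator.

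**Working it through.** **Inputs.** All are from VIII.C, step 7: s = 10,000; p = 0.10; m = 2.

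**1. The printed figure.** E = 10,000 × 0.9 + 10,000 × 0.1/2 = 9,000 + 500 = 9,500. The arithmetic reproduces.

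**2. Forward check under the printed definition of p.** Take N women, of whom a proportion p use m sites on average and the rest use one. Assume that each multi-site woman is counted at all her sites. The site counts then sum to

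s = N(1-p) + N*p*m = N[1 + p(m-1)].

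With N = 9,500 this gives 9,500 × 0.9 + 9,500 × 0.1 × 2 = 8,550 + 1,900 = 10,450 counts, not the 10,000 of the example. Likewise, the 9,500 is made up of 9,000 single-site and 500 multi-site women, so the multi-site share is 500/9,500 = 5.3%, not 10%.

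**3. The estimate consistent with that definition.** N = s/(1 + p(m-1)) = 10,000/1.1 = 9,091. Check: 9,091 × 0.9 + 9,091 × 0.1 × 2 = 10,000 after rounding.

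**4. Size of the difference.** The ratio of the printed formula to N is

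[(1-p) + p/m] × [1 + p(m-1)] = 1 + p(1-p)(m-1)^2/m,

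which exceeds 1 whenever 0 < p < 1 and m > 1. In the example it is 1 + 0.1 × 0.9 × 1/2 = 1.045, an excess of 409 women (4.5%). The protocol gives no other values of p and m. For assumed values the same factor gives:

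| p (assumed) | m (assumed) | Excess |
|---|---|---|
| 0.1 | 3 | 12.0% |
| 0.3 | 2 | 10.5% |
| 0.3 | 3 | 28.0% |

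**5. When the printed formula is exact.** Let p be the share of site counts contributed by multi-site women. When 10% of women use two sites, that share is 0.2/1.1 = 0.1818. The printed formula then returns 10,000 × 0.8182 + 10,000 × 0.1818/2 = 9,091, in agreement with step 3.

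**6. The two meanings of m.** If 10% of women use two sites and the rest use one, the mean over all women is 0.9 × 1 + 0.1 × 2 = 1.1. Put into the printed formula, this gives 9,000 + 1,000/1.1 = 9,909, which is 9.0% above 9,091. The example's m = 2 is a different quantity from the m defined above it.

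**7. Sensitivity to the counting assumption.** The site counts come from informants' estimates for a busy time, so a woman who uses two sites on different nights need not be in both. If only a fraction c of the two-site women are counted twice, N = 10,000/(1 + 0.1c):

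- c = 1: 9,091
- c = 0.526: 9,500
- c = 0: 10,000

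**The case against.** The strongest reply is that p was meant as a share of counts. The example can be read as splitting the 10,000 site-level total into 90% and 10%, and on that reading 9,500 is correct. People interviewed at venues (Form C, item C4) over-represent those who visit many places, so their unweighted answers would lie nearer a count share. But the printed definition of p is a proportion of women, and the PLACE analysis section plans weights aimed at population estimates. This reply shows that the definition needs changing. It does not make the text consistent.

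The second reply is that counting at every site is an assumption. This stands. The text says only that people might be counted more than once. 9,091 is therefore the full-duplication limit, and 9,500 would be right if about 53% of the two-site women were counted twice. With less duplication than that, 9,500 would be too low.

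The third reply is that the example's wording makes the intended m clear. It probably does, but the definition should then say the same.

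A reader might also infer three stronger points that the document does not support:

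- **Every coverage figure is biased.** Most coverage indicators in Table 4 divide by people interviewed or respondents, and those do not use the size estimate.
- **The final size estimate is inflated by a known amount.** Step 6 also adjusts for visits to more than one site in a day, and further steps add missing members and extrapolate. The net bias is not established.
- **Sampled venues are never scaled up.** Table 3 does say "If there are more than 700 venues are identified in Luanda, a sample of venues will be selected", but step 3 recognises that the site types have different sampling fractions, and explicit expansion factors may properly be left to an analysis plan.

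**Conclusion.** The mismatch is real on the printed definitions. A person-level p is applied to a sum of counts, and m is defined over all women but used for the multi-site women. If multi-site women are counted at each of their sites, the printed formula is too high by the factor 1 + p(1-p)(m-1)^2/m, which is 4.5% in the protocol's own example (9,500 against 9,091). Larger excesses need values of p and m that the protocol does not give. The direction and size also depend on how completely multi-site women are duplicated in busy-time counts. The formula stands as printed only if p is redefined as a share of site counts. The effect is confined to the size estimates and whatever uses them as denominator.

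A separate and minor slip: the venue informant row of Table 3 adds to 700 + 500 + 500 + 500 = 2,200, not the printed 1,500.

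**What to change.** Choose one of two consistent versions of step 7:

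1. Use E = s/(1 + p(m-1)), with p a person-level proportion estimated with attendance weights.
2. Keep the printed formula and define p as the share of site-level counts that come from multi-site women, estimated with the site selection weights. A raw share of interviewed people will not do, because sites are drawn in proportion to size and social mobilisers point out key-population members for interview.

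In both versions:

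- define m as the mean among multi-site women of the number of sites at which they would be counted in the same reference period as s;
- make the worked example match: 9,091 if the 10% is person-level, 9,500 if it is a share of counts;
- state that step 6 does not correct the same duplication again;
- correct the Table 3 venue total to 2,200.

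The cost is one formula or definition, one example and a few sentences. The data need a check. The items on other places visited (Form B, B3B; Form C, C4) cover a single day and include places visited to socialise or drink, so they do not directly measure the number of sites at which a woman solicits. Either the wording of an item or the way it is used for p and m may have to be adapted.
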